##### Sample size estimation

Power was computed for a natural experiment evaluation (NEE) using Difference-in-Difference (DiD) analysis. For Aim 1, we calculated sample size for a Type I error rate alpha of 0.05, power of 0.8 for comparing the means between two groups considering physical activity outcomes of moderate-to-vigorous physical activity (MVPA); light, moderate, and vigorous physical activity (LMVPA); and time spent in sedentary behavior. Prior research has shown observed effects of moving to an activity-friendly community ranging between 10.4–10.9 min/day of MVPA, indicating small effect sizes of 0.40–0.42 (Cohen’s D) (7). We conservatively powered this study to detect a smaller effect size (Cohen’s D = 0.35). We estimate a sample size of 129 per group will provide adequate power to detect an effect size of Cohen’s D = 0.35 for all physical activity outcomes. The effect size of 0.35 is a conservative estimate based on current literature, equating to minimal detectable differences between 7.9 and 9.6 min/day for MVPA using estimates of standard deviation from previous studies (7, 33–37). This sample size is also adequate for a minimal detectable difference of 13.3 min/day for LMVPA. This sample size is adequate to detect effect sizes that are small to medium for all outcomes based on calculations for other aims. Prior community sampling of an NEE examining accelerometer-measured MVPA found a 20.64% attrition rate from baseline to year 1 and a 6.63% attrition rate from year 1 to year 2 (33). Given recently reported challenges to NEE recruitment, we conservatively overestimate attrition rates, necessitating a sample size of 175 for the agrihood and comparison groups.

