##### Loss to follow-up

A participant will be considered lost to follow-up if they fail to return for any of the scheduled follow-up visits, or do not complete that timepoint’s survey, and cannot be contacted by the research team by the end of the study period. In the case of loss to follow-up or withdrawal, partial data will be used in the data analysis with multiple imputation used to address missing data where appropriate. Intent-to-treat will be used to preserve the group allocation in our analysis (38).

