### Data analysis

For Aim 1, we will compare the changes in physical activity outcomes (moderate to vigorous physical activity [MVPA], light, moderate, and vigorous physical activity [LMVPA], walking, sedentary behavior) between the agrihood and comparison participant groups across three time points (Agrihood: pre-move-in, 3 months after move-in date, 6 months after move-in date; Comparison: 0, 3, 6 months) using DiD analysis (linear mixed-effects longitudinal models). Regression models will include the group, time period, and the group by time period interaction terms. Random cluster effects will be included to account for correlations between participants in the same neighborhood and *a priori* covariates of age, sex, and educational attainment. Random effects for the participants will be included to account for correlation in observations. To address multicollinearity, we will assess variance inflation factors (VIF > 5) and pairwise correlations (|r| > 0.70); collinear variables will be excluded, combined, or tested in sensitivity analyses to avoid attenuation of the group × time effect. Confounders showing baseline imbalance (standardized mean difference > 0.10) will be prioritized for inclusion. Restricted maximum likelihood will be used for complete case analysis to incorporate all available data, and intention-to-treat analysis will include all participants included at baseline. Multiple imputation will be used to estimate missing data points and standard errors. Imputations will follow standardized procedures, including auxiliary variables, and will follow hierarchical approaches. We will examine the potential for missingness of data to not be at random by comparing baseline characteristics of participants who have completed physical activity data with those who do not. If there are differences by age, education, race, or self-reported perceived health, any variables that differ will be used as an auxiliary variable in multiple imputation. Fraction of missing information will be used to measure level of uncertainty about the values imputed for missing values. We will use a number of imputations that satisfy the recommendation to have the number of imputations (at least) equal the highest fraction of missing information (FMI) percentage. Using the geographic information system (GIS) data and resulting maps, for physical activity resources we will: (1) count the number of resources located within the 5-mile network buffer using ArcGIS; (2) measure the distances to the closest resources for different types of resources (e.g., closest park or trail) using ArcGIS and Google Distances API; (3) assess how these counts and distances change over time; and (4) assess changes in time spent in transportation to go to resources. Specifically, we will compare the changes in number of physical activity resources, distance (in miles) to closest objectively measured resources, and distance (in miles) to utilized resources and associated transportation-related time spent between the groups across 3 time points (Agrihood: 0, 3 months after move-in date, 6 months after move-in date; Comparison: 0, 3, 6 months) using DiD analysis, and assess if any of these variables are associated with device-measured physical activity outcomes using linear mixed-effects multilevel models. All statistical analysis will be conducted using SAS and/or R software. We will also generate maps showing changing patterns in physical activity resource utilization in ArcMap. This two-pronged approach of mapping and analyzing objective physical activity environments as well as physical activity resource utilization and time use behaviors are important to better understand how the built environment in these communities are or are not conducive to physical activity, as well as how participants are (or are not) engaging in the resources designed to promote physical activity.

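### The missing-data text calls the REML model a complete-case analysis that also uses all available data, and its check for not-at-random missingness cannot detect it

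*Protocol article*

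**What the plan says.** All of this is in the protocol article.

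- **Fitting method and analysis set** (Data analysis, Aim 1): "Restricted maximum likelihood will be used for complete case analysis to incorporate all available data", and in the same sentence "intention-to-treat analysis will include all participants included at baseline".
- **Imputation** (next sentence of that section): "Multiple imputation will be used to estimate missing data points and standard errors". The text adds that auxiliary variables are part of the imputation procedure and that it will be hierarchical.
- **People who leave** (Loss to follow-up): "partial data will be used in the data analysis with multiple imputation used to address missing data where appropriate".
- **Check on the missingness mechanism** (Data analysis): "We will examine the potential for missingness of data to not be at random by comparing baseline characteristics of participants" with and without completed physical activity data. If age, education, race or perceived health differ, "any variables that differ will be used as an auxiliary variable in multiple imputation".

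The Data analysis section then applies the same strategy to food sourcing and dietary intake, so the wording governs more than physical activity.

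**The concern.** There are two separate problems, and both lie in what the text states.

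**Analysis set.** A complete-case analysis drops a participant who misses a visit. A mixed model fitted by REML to all available records keeps that participant's observed visits. The two also need different assumptions. The likelihood analysis is valid under MAR given what is in the model, while complete-case analysis generally needs something stronger. One fit cannot be both, and an analyst could follow either phrase.

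**Check.** MNAR means that missingness depends on unobserved values even after conditioning on what was observed. A comparison of observed baseline variables carries no direct information on that. If it is read as the plan frames it, a clean comparison could be taken as evidence against MNAR when it is not. A positive comparison leads only to a step that is itself valid under MAR.

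Attrition matters here, because the Discussion says that more than the usual amount was expected and allowed for.

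**Working it through.** **1. Reproduce the plan's sample size** (Sample size estimation)

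Inputs: "Type I error rate alpha of 0.05, power of 0.8 for comparing the means between two groups"; d = 0.35; 129 per group; 175 enrolled per group; attrition of 20.64% to year 1 and then 6.63% to year 2. Sidedness is not stated; I assume two-sided.

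- n per group = 2(1.960 + 0.842)² / 0.35² = 128.1, rounded up to 129. Power at 129 is 0.803.
- Cumulative attrition = 1 − (1 − 0.2064)(1 − 0.0663) = 25.9%. Then 129 / 0.741 = 174.1, rounded up to 175.
- Attrition implied by the two sample sizes = 1 − 129/175 = 26.3%.

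Both figures reproduce, so the sample size is not in dispute.

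**2. How far apart the two analysis sets are**

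- Complete cases at planned attrition: about 129 per group.
- Everyone with a baseline: 175 per group.
- Difference: 175 − 129 = 46 per group, or 26.3%.

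The attrition rates used are two-year rates from an earlier study and follow-up here is 6 months, so the realised gap may be smaller. Even on the complete-case reading the planned power of about 0.80 would hold, because 129 is the number the study was sized on. What changes is the population analysed and the assumption needed.

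**3. Set the statements side by side**

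| Statement | Set implied |
|---|---|
| Complete case | Only those with no missed visit |
| All available data | Every observed record |
| Intention-to-treat set | Everyone at baseline |
| Multiple imputation | Everyone, missing values filled in |
| Partial data used after loss or withdrawal | Every observed record |

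Only the first conflicts with the rest.

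**4. What the baseline comparison can see**

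I ran an illustrative simulation with assumed parameters: 350 people in two equal groups, one observed baseline covariate x, outcome y = 0.3x + u with u independent of x and SD 1, true group difference 0, and 2,000 runs. The check was a t-test of x between those with and without outcome data. The estimate was the group difference adjusted for x in those observed.

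| Mechanism (logit of missingness) | Missing | Check significant | Mean estimated difference (truth 0) |
|---|---|---|---|
| MCAR (−1.03) | 26.2% | 5.5% | 0.002 |
| MAR (−1.1 + 0.6x) | 26.5% | 99.85% | −0.004 |
| MNAR, agrihood only (−1.15 − 0.8u) | 25.3% | 4.6% | 0.188 |

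The check fires where adjustment already removes the bias. Under this form of MNAR, where bias remains at about 0.19 residual SD, it stays at its nominal error rate. If the unobserved driver were correlated with a compared baseline variable, the check would register part of it, but the result could not be told apart from MAR. The simulation has one follow-up outcome; earlier measurements in a mixed model could recover part of the bias.

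**5. Illustration of what could be at stake**

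Let f be the fraction lost in each group. Let δA and δC be the amounts by which the true change among agrihood and comparison dropouts falls below the MAR prediction. Then the error in the difference-in-differences is f × (δA − δC). With f = 0.263:

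| δA − δC, in units of the planned detectable difference | Error, same units |
|---|---|
| 0 (same selectivity in both groups) | 0 |
| 0.5 | 0.13 |
| 1 | 0.26 |

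In the plan's MVPA units (7.9 to 9.6 min/day) the last row is 0.263 × 7.9 = 2.1 to 0.263 × 9.6 = 2.5 min/day. The minutes are only a guide: the attrition source was accelerometer-measured MVPA, and comparison participants wear no accelerometer (Data collection; Discussion).

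**The case against.** The strongest reply is that four statements point to using everyone and only the complete-case label does not, so the label is probably a slip for available case. That stands. A reader might infer that the plan's main analysis is complete case and discards a quarter of the cohort. The article names no main analysis, and its other statements exclude that reading. What is left is a contradiction that the authors must correct, because the text as printed permits both.

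On the check, the text says only that the potential for non-random missingness will be examined. Using variables that differ as auxiliaries is sound under MAR. That also stands, and nothing says a null result will be reported as reassurance. The error is the purpose attached to the comparison.

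Three further inferences are not supported:

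- **That auxiliaries are chosen only by whether they differ.** The section separately plans auxiliary variables in the imputation, and age and educational attainment are covariates fixed in advance. The comparison is not described as the only gate.
- **That the planned analyses will overstate benefit by 2.1 to 2.5 min/day.** This needs selective dropout confined to the agrihood group, a shortfall of one full detectable difference, two-year attrition within 6 months, and accelerometer figures that the comparison group cannot supply. Similar selectivity in both groups would largely cancel.
- **That the lack of an MNAR sensitivity analysis is an omission.** An analysis plan that is not shown may contain one. It is proposed here only because the article states an aim that its chosen method cannot meet.

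**Conclusion.** The point holds on two counts. First, the REML sentence contradicts itself, the intention-to-treat set and the Loss to follow-up section. The competing sets differ by up to about 46 of 175 per group, if the planned attrition of 26.3% is realised. Second, the comparison of observed baseline characteristics is given a task that it cannot perform. It bears on MCAR, and it neither detects nor excludes MNAR; this follows from the definitions and does not depend on the simulation parameters.

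The importance is moderate. Sample size, data collection and the probable estimator are unaffected. Any bias figure is an illustration, conditional on dropout that is selective and differs between groups.

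**What to change.** 1. In Data analysis, delete the complete-case label. State that the REML mixed model uses every available record of all participants with a baseline, and bring Loss to follow-up into line.
2. Describe the comparison of participants with and without physical activity data as a check on MCAR and a source of auxiliary variables under MAR.
3. For the stated purpose of examining not-at-random missingness, use a delta-adjusted (pattern-mixture) sensitivity analysis on the imputations already planned. Shift the imputed follow-up values over a range of deltas, allow different shifts in the two groups, and report the tipping point at which the conclusion changes.

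The cost is a few sentences of text and one extra sensitivity run on data already being collected. No new measurements or participants are needed.

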## Discussion

Consuming a healthy diet and being physically active are crucial for preventing, managing, and improving chronic diseases, yet many communities lack access to fresh foods or safe spaces for physical activity. Neighborhood built environments, particularly those that integrate agricultural production, can be intentionally designed to facilitate walkability, healthy food purchasing, and social interaction. With more than 200 planned or developed agrihoods across the country, a need has been identified for rigorous, longitudinal evaluations to better understand the impact these neighborhoods have on residents’ health and surrounding economies. The present paper details our scalable protocol for a naturalistic study in Fort Bend County, Texas.

By combining two longitudinal cohorts of matched residents, we will address three specific aims with the following expected outcomes based on our team’s experience and formative research. First, from Aim 1 (assessing short-term changes in dietary intake, physical activity, cardiometabolic health indicators, and social connectedness), we expect to demonstrate how physical activity and sedentary behaviors and locations change for adults who relocate to the agrihood compared to adults who do not. We will examine the impact of relocating to the agrihood on MVPA, LMVPA, walking, and sedentary behavior, and expect to find changes in physical activity resource utilization. We expect to explain how living in the agrihood impacts social connection and determine how connection relates to physical activity and healthy eating among participants across time. With this newly generated knowledge, we will be able to more fully explain the dynamic relationship between social connection, built environment, and chronic disease prevention. From exploratory Aim 2 (documenting time use with features of the agrihood and assessing consumer preferences for built and nature design features to provide resident-driven data for future developments), we expect to describe how residents utilize the various features of the agrihood and how much time they spend engaging in these features of their neighborhood. Finally, from exploratory Aim 3 (assessing the economic benefits of the agrihood), we expect to describe resident and developer perspectives of the cost-efficiency of living in and running an agrihood and agrihood farm model.

Our study design has several strengths, including multiple matched cohorts of residents. In addition, we propose a strong data-driven approach involving biological data collection from the mobile health assessment clinics and device-captured physical activity, along with highly valid and reliable self-report measures that capture individual and community-level preferences and perspectives. Given our multi-disciplinary team and established partnerships with the developers, we anticipate the aims will be achievable, and the results generated from this work will translate into meaningful considerations for residents of these neighborhoods. Moreover, we believe the results will allow us to understand not only how agrihoods affect health and wellbeing, but also how residents engage with them, thereby informing future models for development that are effective for improving health and are economically sustainable.

Given funding and scope of work parameters, this study also has several limitations worth noting. First, the comparison community consists of existing residents, meaning we are unable to capture their baseline prior to moving in, unlike with the agrihood participant sample. Capturing residents as they move into a new development is extremely challenging, and it was not feasible to find a comparison community that was being occupied at the same time as the agrihood. Second, due to budgetary constraints, accelerometer-based physical activity measurement and biological data collection are only feasible among participants in the agrihood community, which may reduce cross-group comparability. Third, the funding support received for this work only covers 13 months, thereby allowing for 6 months of follow-up which may be too short to observe meaningful or sustained behavioral and health changes.

Additional challenges may arise with retention from recruitment events to follow-up in-person physical assessments. The MHACs are based in Dallas, Texas, and our team has limited days for on-site biological data collection, which may create scheduling barriers. To mitigate this, participants will be offered flexible options such as completing online surveys remotely and receiving accelerometers by mail or at a designated community pick-up location (the Filling Station). Higher-than-usual attrition was anticipated and accounted for in our study design. The protocol also allows for multiple adults (e.g., married couples) within the same household to participate. This decision was made to help achieve recruitment and enrollment goals given the number of households under contract. Interclass correlations within households will be accounted for statistically in the analysis.

For cholesterol and HbA1c data, we are using finger prick sampling rather than venipuncture. Although venipuncture is often considered more precise, capillary testing has been shown to produce comparable results when performed properly and is substantially less invasive and more acceptable in community-based research settings (41–45). Self-reported survey data also introduce potential recall and social desirability bias. The economic analysis component is exploratory, drawing on developer-provided data and resident perceptions. While this approach supports early feasibility insights, it limits the ability to conduct standardized cost–benefit or return-on-investment modeling. Future work will incorporate objective financial metrics (e.g., property values, healthcare cost offsets) to strengthen policy and planning relevance.

Finally, this study is limited to one agrihood in a single region (Fort Bend County, Texas), which may restrict generalizability to other cultural, climatic, or socio-economic contexts. Despite these limitations, this pilot study represents a critical first step in establishing the feasibility, logistics, and interdisciplinary partnerships needed for more rigorous future work. The present phase provides foundational data to inform a larger, multi-site randomized controlled trial with extended follow-up, expanded objective data collection, and greater diversity among participants.

In conclusion, agrihoods present an innovative and relatively novel idea for building healthier communities. As people have reduced outdoor time and moved away from farms over the last few decades, many are now disconnected from nature and the process of growing food (46). If this study is successful, it may provide evidence of the health benefits of this type of urban design and help to shape future neighborhoods. Like all natural experiments, this research design does have some limitations. These are counterbalanced by a high level of external validity. The data collection methodologies are solid and provide short-term indications of changes in biological indicators and health behaviors. We will actively seek funding to include 12- and 24-month follow-ups, as well as to support future scale-up to larger evaluations and the development of interventions and initiatives informed by the findings from the present study.
